#### 2.11.2 Mediation analyses

We will compute pre–post change scores for all process measures in the study and pre–follow-up change scores for primary and secondary outcomes. Bivariate Pearson correlations will be calculated between the pre–post change scores for the process variables and the pre–follow-up change scores for the clinical endpoints to detect statistically significant relationships. The direct and indirect associations between the treatment condition (i.e., FIBRO-On vs. TAU, FIBRO-Out vs. TAU, or FIBRO-On vs. FIBRO-Out, as independent variable), process variables (mediators), and primary and secondary outcomes (dependent variables) will be computed by using path analyses. With this statistical approach, we are considering temporality into account, which increases the prospect of establishing conclusions about causality. Simple and multiple mediation (simultaneously testing multiple variables as mediators) models will be computed.

Similarly, for obtaining more detail about psychological mechanisms fostered during intervention and its role in the observed effect at post-intervention, mediation analyses will also be conducted by using change scores of process measures between baseline and 6-week assessment and change scores for clinical measures between baseline and post-intervention assessments. The direct paths between treatment condition and clinical outcomes and the indirect effect path through the mediation variables will be tested in all the models. Regression coefficients (B) of bias-corrected bootstrapped indirect effects will be calculated as well as their SEs and 95% CIs (Lockhart et al., 2011). Parameters of indirect effects are considered statistically significant when the 95% CI did not include 0. Participants with missing data will be excluded for this analysis.

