The objectives of the On&Out study are 1) to examine the effectiveness and cost-utility of adding the FIBROWALK intervention in online or in outdoors format to TAU in the management of patients with FM for improving functional impairment (primary outcome) and pain, fatigue, depressive and anxiety symptoms, perceived stress, central sensitization, physical function, sleep quality and perceived cognitive dysfunction (secondary outcomes); 2) to identify pre–post differences in levels of different physiological variables (i.e., immune-inflammatory markers and BDNF levels) and correlate these changes with those observed at self-report measures and 3) evaluate the role of psychological process variables considered to be potential mediators of the interventions from a theoretical point of view (i.e., kinesiophobia, pain catastrophizing, psychological inflexibility in pain and pain knowledge) and the evaluated physiological variables as mediators of long-term clinical improvements. For the sake of personalized treatment in FM, the design of the present study will allow us to explore whether certain patient profiles or baseline psychobiological characteristics may help predict the short- and long-term clinical response to the specific evaluated treatments.

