### 2.3 Sample size calculation

Two-hundred and twenty-five individuals who meet the selection criteria for the study will be recruited. The estimated sample size needed is n = 63 participants per condition considering a moderate effect size (Cohen’s d = 0.5) for the difference between the active arms at post-intervention compared to the control group for the primary variable (i.e., FIQR score) with an alpha = 0.05 and 1-b power = 0.80. With an expected dropout rate of 20%–25%, the final sample size is estimated at 75 individuals per arm. The effect size used for the sample size calculation corresponds to the average effect size for multicomponent interventions in FM vs. control group (Nüesch et al., 2013). Previous RCTs evaluating the FIBROWALK intervention indicated effect sizes between d = 0.4 (Serrat et al., 2021a) and d = 1.83 (Serrat et al., 2020). Using as a reference previous studies of the group evaluating the effect of different non-pharmacological treatments in FM patients on blood values of immuno-inflammatory markers (Andrés-Rodríguez et al., 2019; Montero-Marin et al., 2020), it is estimated that a sample size of 40 subjects per arm will be sufficient to be able to detect changes in the evaluated variables.

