The On&Out study will also evaluate the effect of the FIBROWALK multicomponent programs on immuno-inflammatory markers and BDNF levels that seem to be altered in FM and/or play a role in the effectiveness of non-pharmacological treatments (Rodriguez-Pintó et al., 2014; Andrés-Rodríguez et al., 2019; Montero-Marin et al., 2019). It should also be noted that, to date, the effect of any multicomponent program on such biomarkers in FM has not been evaluated by means of a RCT design. Furthermore, the evaluation of changes in these biomarkers and their association with clinical change will further deepen the understanding of the role of the immune system and neuroprotective agents in FM and related disorders cursing with central sensitization. Associated with this substudy of the project, it should be noted that the inclusion of biomarkers may also make it possible to determine different patient profiles (based on their psychobiological characteristics) which could be predictive of a greater or lesser response to the treatments under study. This aspect is fully connected with the emerging field of personalized treatments and can contribute to optimizing the use of healthcare services while also enhancing the efficacy and cost-effectiveness of the interventions evaluated (Thase, 2014; Lopresti, 2017; Carvalho et al., 2019).

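### The correlations between process change and clinical change make no allowance for arm, so if pooled they can show a relationship that comes only from treatment shifting both variables

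*Protocol article*

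**What the plan says.** Section 2.11.2 opens with change scores: baseline to post-intervention for the process measures, and baseline to 6-month follow-up for the clinical outcomes. It then states: "Bivariate Pearson correlations will be calculated between the pre–post change scores for the process variables and the pre–follow-up change scores for the clinical endpoints". The declared purpose is "to detect statistically significant relationships". No covariate, partialling or by-arm calculation is mentioned, and the article does not say explicitly whether the arms are pooled.

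The same section goes on to path analyses of these change scores. There, treatment is the independent variable, as pairwise contrasts: "i.e., FIBRO-On vs. TAU, FIBRO-Out vs. TAU, or FIBRO-On vs. FIBRO-Out, as independent variable), process variables (mediators". It adds: "The direct paths between treatment condition and clinical outcomes and the indirect effect path through the mediation variables will be tested in all the models". The correlations are not said to decide which mediators enter those models.

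For biomarkers, objective 2 (end of section 1.3) promises to "correlate these changes with those observed at self-report measures". The Discussion (section 3) says that "the evaluation of changes in these biomarkers and their association with clinical change will further deepen the understanding of the role of the immune system". Section 2.11.4, on biomarker changes, gives no method for this association.

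**The concern.** A correlation computed over the whole sample reflects the total covariance. That is the covariance within arms plus the covariance of the arm means. With 1:1:1 allocation, two thirds of participants receive a programme meant to improve both the process variables and the clinical outcomes. If it does, the arm means of both variables move together and the pooled correlation is non-zero. This holds even if participants whose process score changed more did no better clinically than others in the same arm.

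A reader of the results would take a significant correlation to mean that individual change in, say, catastrophizing goes with individual clinical improvement. Part or all of it could simply restate that both variables responded to treatment. The larger the treatment effect, the more often this happens.

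**Working it through.** **Inputs from the protocol article**
- Allocation 1:1:1 (section 2.5); 75 per arm, dropout 20%–25%, alpha 0.05 (section 2.3).
- Planning effect, for FIQR at post-intervention: "considering a moderate effect size (Cohen’s d = 0.5) for the difference between the active arms at post-intervention compared to the control group".
- Earlier trials: "Previous RCTs evaluating the FIBROWALK intervention indicated effect sizes between d = 0.4" and d = 1.83. Section 2.3 attaches these two values to two different trials, which sections 1.1 and 2.6 identify as the online and the outdoor format.
- Complete cases only for the mediation analyses (section 2.11.2).

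**The plan's own figure.** n per arm = 2(1.96 + 0.842)² / 0.5² = 62.8, so 63. The stated 63 reproduces, which confirms 0.5 SD as the planning effect. The correlation step has no stated figure of its own.

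**Assumptions.** The documents give no effect size for process variables. Shifts are therefore assumed, in SD units of the change score. Within-arm correlation is set to zero, data are normal, and TAU has shift 0. Evaluable number: taking 22.5% loss, the middle of the stated range, 75 × 0.775 ≈ 58 per arm, 174 in all.

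**Expected pooled correlation.** With equal shifts dm (process) and dy (outcome) in both active arms, the between-arm covariance is (2/3)(1/3)·dm·dy = (2/9)·dm·dy. So

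r = (2/9)·dm·dy / √[(1 + (2/9)dm²)(1 + (2/9)dy²)].

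- 0.4 SD on both: 0.0356 / 1.0356 = 0.034
- 0.5 SD on both: 0.0556 / 1.0556 = 0.053
- 0.8 SD on both: 0.1422 / 1.1422 = 0.125

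For a process shift of 0.5 in both active arms and outcome shifts of 0.4 (online) and 1.83 (outdoor):
- means are 0.333 and 0.743
- covariance = (0.5 × 0.4 + 0.5 × 1.83)/3 − 0.333 × 0.743 = 0.124
- between-arm variances are 0.0556 and 0.617
- r = 0.124 / √(1.0556 × 1.617) = 0.095

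**Simulated rejection rate at nominal 5%, 174 evaluable**

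| Process shift | Outcome shift | Unadjusted Pearson | Adjusted for arm |
|---|---|---|---|
| 0 | 0 | 5% | 5% |
| 0.4 | 0.4 | about 7% | 5% |
| 0.5 | 0.5 | about 11% | 5% |
| 0.8 | 0.8 | about 37% | 5% |
| 0.5 | 0.4 online, 1.83 outdoor | about 24% | 5% |

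Repeat runs agree to about one percentage point.

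**Sensitivity.** With 63 to 75 evaluable per arm, the unadjusted rate is 8% at 0.4 SD, 11% to 12% at 0.5 SD and 40% to 47% at 0.8 SD. Pooling only two arms (one active, one TAU) does not remove the problem: at 0.5 SD it gives r = 0.059 and 10% to 11%. Adjustment for arm gives 4.7% to 5.2% in every scenario with these numbers.

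**The case against.** The strongest reply is that the same section relates the same change scores in path models that include treatment and its direct path to the outcome. The path from mediator to outcome is therefore already adjusted for arm, and the indirect effects are judged by bootstrap intervals, not by these correlations. This stands. A reader might infer that the mediation conclusions are unsound, or that the correlations screen the mediators. The documents support neither.

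Second, pooling is not stated, and an article may leave such detail to a fuller plan. The first half is true. But the article names a specific test and gives it an inferential purpose; bivariate means that arm is not in it. One clause would settle the matter if by-arm correlations are intended.

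Third, a non-zero pooled correlation is a real feature of the total sample, so rejecting zero is not an error for that quantity. This holds if the result is read as description. It does not hold if the result is read as a relation between one participant's process change and that participant's clinical change.

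Fourth, the size depends on assumed shifts. This also stands. The planning d is for FIQR at post-intervention and section 2.11.1 standardises by baseline SD, whereas the shifts here are in change-score SD and the outcome is at 6 months. Giving 1.83 to both active arms would yield about 51% instead of 24%, but section 2.3 takes that value from the outdoor trial alone.

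Finally, a reader might infer that the article fixes an unadjusted test for biomarkers. It does not: it says only that changes will be correlated and speaks of an association. The documents also give no biomarker effect size.

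**Conclusion.** The point holds in limited form. As written, the process–outcome correlations make no allowance for arm and, if pooled, can show a relationship created only by treatment. At the planning effect the induced correlation is small (about 0.05) and rejection roughly doubles, from 5% to 11%. About 89% of such trials would show nothing significant. The excess becomes serious only with larger shifts: about 37% at 0.8 SD on both variables, or about 24% with the online and outdoor effects that the article cites and a 0.5 SD process shift.

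These figures rest on pooling across arms, no within-arm relation, and shifts that the documents do not supply for process variables. The primary FIQR analysis and the bootstrapped indirect effects are not affected. For biomarkers the gap is a missing method, not a wrong one. This is a minor point, worth correcting because the correction is nearly free.

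**What to change.** In section 2.11.2, replace the bivariate correlations with partial correlations adjusted for arm (two indicator variables) or with pooled within-arm correlations, and report these as the association result. State the same method for the biomarker and self-report correlations of objective 2, most naturally in section 2.11.4. If unadjusted correlations are still shown, label them descriptive and attach no significance claim to them.

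The cost is two degrees of freedom per correlation and a small change to the analysis code. No further data are needed, and the sample size and the path models stay as they are.

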### 2.8 Study measures

Assessment of outcome and process measures will be carried out at baseline, 6 weeks after starting treatment, at post-intervention (12 weeks) and at 6-month follow-up after starting the trial (follow-up. Cost-utility assessment will be conducted at baseline and at the follow-up and biomarkers evaluation at baseline and post-intervention. The research assistants in charge of the evaluations will be extensively trained by researchers (MS, [name]), who have broad experience in applying the study measures.

The following domains will be assessed (see Table 3 for a summary of assessments):- Socio-demographic questionnaire: gender, date of birth, marital status, cohabitation, educational level and employment status.- Clinical data: date of FM diagnosis, years with a FM diagnosis, comorbidity with other diagnosed medical/psychiatric conditions, type and dosage of current medication, weight and height.

**TABLE 3 T3:** Summary of the assessments in the RCT.

	Baseline	6 weeks	Post-intervention (12 weeks)	Follow-up (6 months)
Sociodemographic and clinical characteristics of the sample				
Sociodemographic data	X			
Clinical data	**X**			
Primary outcome measure				
FIQR	**X**	**X**	**X**	**X**
Secondary outcome measures				
VAS Pain	**X**	**X**	**X**	**X**
VAS Fatigue	**X**	**X**	**X**	**X**
HADS	**X**	**X**	**X**	**X**
PSS	**X**	**X**	**X**	**X**
PF-SF-36	**X**	**X**	**X**	**X**
B-PSQI	**X**	**X**	**X**	**X**
MISCI	**X**	**X**	**X**	**X**
CSI	**X**	**X**	**X**	**X**
PGIC/PSIC			**X**	
Process measures				
PCS	**X**	**X**	**X**	**X**
TSK-11	**X**	**X**	**X**	**X**
PIPS	**X**	**X**	**X**	**X**
R–NPQ	**X**	**X**	**X**	**X**
Cost-utility measures				
CSRI	**X**			**X**
EQ-5D	**X**			**X**
Other self-reported measures				
CEQ	**X**		**X**	
Perceived adverse effects of the interventions		**X**	**X**	
Fidelity evaluation (adherence of the therapists to the FIBROWALK guidelines)			**X**	
physiological markers				
Immune-inflammatory markers	**X**		**X**	
BDNF	**X**		**X**	

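### The mediation models nest the mediator's change window inside the outcome's, so they do not separate concurrent from subsequent change and cannot carry the temporality claim

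*Protocol article*

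**What the plan says.** Section 2.11.2 computes "pre–post change scores for all process measures in the study and pre–follow-up change scores for primary and secondary outcomes". Pearson correlations are calculated "between the pre–post change scores for the process variables and the pre–follow-up change scores for the clinical endpoints", and path models then link arm, process variables and outcomes. A second set of models pairs "change scores of process measures between baseline and 6-week assessment" with "change scores for clinical measures between baseline and post-intervention assessments". The stated gain is that "we are considering temporality into account, which increases the prospect of establishing conclusions about causality".

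The decision rule uses bias-corrected bootstrap intervals: "Parameters of indirect effects are considered statistically significant when the 95% CI did not include 0". On missing data: "Participants with missing data will be excluded for this analysis".

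Section 2.8 places assessments at baseline and "6 weeks after starting treatment, at post-intervention (12 weeks) and at 6-month follow-up after starting the trial". Table 3 shows FIQR, the symptom scales and all four process measures at every one of these times. Section 2.10 plans the same structure for the biomarkers, with pre–post change as mediator of 6-month clinical change.

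**The concern.** In both sets of models the two change scores start together, and the outcome window contains the whole mediator window. The protocol expects the clinical effect by week 12: section 2.3 sets the effect size at post-intervention, and the Discussion asks whether effects are maintained at 6 months. If so, much of the 0–6-month outcome change has already happened when the 12-week mediator is recorded. The mediator–outcome path then largely reflects two things changing together. Function improving first and catastrophizing falling afterwards would fit as well as the reverse.

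FIQR and the psychological mediators are self-reports collected at the same assessments from participants who know their arm (section 2.13), so a common cause of correlated change is plausible. At stake is the third objective, on mechanisms. The primary FIQR analysis and the sample size are not affected.

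**Working it through.** **Inputs from the protocol.** 75 per arm with 20%–25% dropout (section 2.3) leaves 75 × 0.80 = 60 to 75 × 0.75 = 56 complete cases per arm; 58 is used. The effect is d = 0.5 with alpha 0.05 and power 0.80. The plan's own figure reproduces: 2 × (1.96 + 0.84)² / 0.5² = 62.7, so 63 per arm (two-sided). No figure is given for the mediation analysis.

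**Assumptions, not in the protocol.** Each scale has baseline variance 1, of which 0.6 is stable and 0.4 occasion-specific. True change by week 12 has variance 0.4 and persists to 6 months. Treatment improves mediator and outcome by 0.5 each. The mediator has no effect on the outcome. The correlation of true changes is *rg*, and that of same-day states is *re*.

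**Spurious path.** Within arm, each change score has variance 0.4 + 0.4 + 0.4 = 1.2. Their covariance is 0.4·rg (shared change) + 0.4·re (shared baseline occasion). So b = 0.4(rg + re)/1.2 = (rg + re)/3, and the spurious indirect effect is −0.5·b = −(rg + re)/6.
- Both 0.3: b = 0.20, indirect effect −0.10.
- Both 0.5: b = 0.33, indirect effect −0.17, one third of the 0.5 treatment effect.
- Both 0: zero, so no bias.

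**Chance of declaring mediation, approximated as both paths significant at 5%.** Arm to mediator: SE = √(2 × 1.2/58) = 0.203, z = 0.5/0.203 = 2.46, probability 0.69. Mediator to outcome: SE = √[(1.2 − cov²/1.2)/(116 × 1.2)].
- Both 0.5: cov 0.40, SE 0.0875, z = 3.81, probability 0.97; product 0.67.
- Both 0.3: cov 0.24, SE 0.0910, z = 2.20, probability 0.59; product 0.41.
- Both 0.1: cov 0.08, SE 0.0926, z = 0.72, probability 0.11; product 0.08.
- Both 0: 0.05 × 0.69 = 0.035.

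Simulation of this joint test gave 66% (both 0.5), 38% (both 0.3) and 4%–7% (0 to 0.1).

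**Under the plan's bootstrap rule** (400 simulated trials per row, 400 resamples, Monte Carlo error at most about 2.5 points). The lagged model also adjusts for baseline mediator, baseline outcome and 12-week outcome.

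| rg | re | Planned model | Lagged model |
|---|---|---|---|
| 0 | 0 | 10% | 8% |
| 0 | 0.3 | 20% | 8% |
| 0 | 0.5 | 42% | 13% |
| 0.3 | 0 | 20% | 13% |
| 0.5 | 0 | 44% | 22% |
| 0.3 | 0.3 | 49% | 4% |
| 0.5 | 0.5 | 71% | 4% |

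Adjusting for the two baselines alone does not help: 53% and 77% in the last two rows.

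**When mediation is real but complete by week 12.** With 58 per arm and the joint test, the lagged model detected it in 3%–37% of trials and the planned model in 52%–70%.

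**Exclusion of incomplete cases.** At about 22.5% dropout and 100,000 per arm, with both correlations 0.5 and no mediation, the indirect effect was −0.167 on full data. It was −0.169 with dropout completely at random, −0.162 to −0.163 with dropout depending on the 12-week outcome, and −0.162 with dropout depending on the 6-month change. Over all settings tried, including true mediation, the shift was at most about 4%.

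**The case against.** The strongest reply has four parts.

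First, the mediator is measured before the outcome in both models, and the causal sentence is hedged. That stands. A reader might infer that temporal order is absent; it is incomplete. What is missing is a separation of outcome change before and during the mediator window from change after it.

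Second, the inflation depends on correlations the document does not give, and covariates of the path models may be listed in a fuller plan. A reader might infer that mediation will be declared where none exists. The documents do not support that: with uncorrelated changes and states the estimate is unbiased. The shared element is the baseline occasion, not a shared score, because the instruments differ. The windows themselves, however, are fixed in the text, and so is the credit they are given for temporality.

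Third, a reader might infer that excluding incomplete cases adds selection bias. This is not shown. It depends on why participants drop out, the shift was small in the settings tried, and section 2.11.1 already plans a comparison of completers with non-completers. Loss of information stands, and so does the contrast with the mixed model for effectiveness and the multiple imputation for costs.

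Fourth, a lagged model changes the question: conditioning on the 12-week outcome removes mediation already achieved during treatment, when a 12-week programme would be expected to act. It is also not clean under the null (13% and 22% when only one correlation is 0.5). This stands, and it rules out simply replacing the planned model.

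**Conclusion.** The point holds in this limited form. The planned models can show that mediator and outcome change together. They do not show that mediator change precedes the outcome change it is said to explain, so the temporality statement goes further than the design of the change scores allows.

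With no true mediation, the false-declaration rate is about 38%–71% when both correlations are 0.3–0.5. It is 20%–44% under the bootstrap rule when only one source of correlation is present, and about 4%–10% at correlations of 0–0.1. These rates rest on the assumed variance split, an effect of 0.5 on both variables that persists to 6 months, and 58 complete cases per arm. The direction of the problem follows from the nested windows; its size does not follow from anything in the protocol. On missing data, the supported criticism is lost information and a population that differs from the intention-to-treat analysis.

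**What to change.** 1. Keep the change-score models, and describe their result as association of concurrent change. Limit the temporality sentence accordingly.
2. Add a pre-specified lagged model: 12-week mediator on arm and baseline mediator; 6-month outcome on arm, 12-week mediator, baseline mediator, baseline outcome and 12-week outcome. Do the same from the 6-week mediator to the 12-week outcome, adjusting for the 6-week outcome. Claim temporal ordering only where the lagged model agrees, and state that it is conditional on no unmeasured mediator–outcome confounding.
3. Use full-information maximum likelihood in Mplus, already listed in section 2.11, in place of exclusion. This mainly recovers information from the expected 20%–25% dropouts and brings the population closer to the intention-to-treat analysis.

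The cost is wording and extra model runs; Table 3 already collects every variable needed, and biomarker mediators can be handled in the same way from 12 weeks to 6 months. The downside is that the lagged model tests only the later-period path, has low power and misses most mediation completed by week 12. It should stand beside the planned model, and the plan should say that a null lagged result does not rule out mediation.

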#### 2.11.1 Analysis of clinical effectiveness

The primary effectiveness analysis will be conducted on an intention-to-treat (ITT) basis with the FIQR total score as a primary clinical endpoint (McCoy, 2017) and by linear mixed-effects regressions with restricted maximum likelihood (REML). REML accounts for the correlation between repeated measures for each individual and produces less biased estimates of variance parameters when using small sample sizes or unbalanced data (Egbewale et al., 2014). No imputation of missing data will be conducted, since it has been reported that multiple imputation is not necessary for all types of missing data (missing completely at random, missing at random, and missing not at random) before computing longitudinal mixed model analysis (Twisk et al., 2013). Unstandardized regression coefficients (B) and 95% confidence intervals (95% CIs) will be computed for the ‘group x time’ interaction between groups at 6-week, post-treatment and 6-month follow-up assessments. Cohen’s d will be calculated for each pairwise comparison, using the pooled baseline SD to weight the differences in the pre–post mean values and to correct for the population estimate (Morris, 2008). The rule of thumb for effect size interpretation will be the classical cutoffs for Cohen’s d of 0.20 = small, 0.50 = medium, and 0.80 = large. All secondary clinical endpoints will be analyzed using the same statistical procedure. Benjamini–Hochberg correction for multiple comparisons will be applied to control for false rate discovery (Glickman et al., 2014). All the analyses will be replicated using a “completers” approach including all participants who finished the study, and a per-protocol approach, taking into account only those patients who attended at least 75% of the sessions (9 out of 12).

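### Mediation (section 2.11.2): about 240 indirect effects are each judged by an unadjusted bias-corrected 95% CI, with no primary mediation family

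*Protocol article*

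**What the plan says.** The third objective (end of section 1.3) is to "evaluate the role of psychological process variables considered to be potential mediators of the interventions", namely "kinesiophobia, pain catastrophizing, psychological inflexibility in pain and pain knowledge". The evaluated physiological variables are named as mediators as well.

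Section 2.11.2 sets out the models:

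- **Contrasts:** "i.e., FIBRO-On vs. TAU, FIBRO-Out vs. TAU, or FIBRO-On vs. FIBRO-Out, as independent variable".
- **Outcomes:** "pre–follow-up change scores for primary and secondary outcomes". A second set of models relates mediator change from baseline to 6 weeks to outcome change from baseline to post-intervention.
- **Model types:** "Simple and multiple mediation (simultaneously testing multiple variables as mediators) models will be computed".
- **Interval:** "Regression coefficients (B) of bias-corrected bootstrapped indirect effects will be calculated as well as their SEs and 95% CIs".
- **Decision rule:** "Parameters of indirect effects are considered statistically significant when the 95% CI did not include 0".

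Section 2.11.2 singles out no mediator, outcome, contrast or window as primary and does not call the mediation models exploratory. The only multiplicity statement is in section 2.11.1, straight after the sentence on secondary clinical endpoints: "Benjamini–Hochberg correction for multiple comparisons will be applied to control for false rate discovery".

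**The concern.** The rule is fixed per parameter, and the number of parameters is large. A treatment-to-mediator difference that arises by chance enters the indirect effect for every outcome in the same contrast and window. If that mediator's change correlates with the outcomes, one chance finding can appear as a run of significant indirect effects and look like a coherent mechanism.

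At stake is how far a positive statement under a numbered objective can be trusted. Section 2.11.2 presents the approach as strengthening causal conclusions, and the Discussion hopes that it will point to new therapeutic targets.

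**Working it through.** **The plan's own figure.** The protocol gives no error rate for mediation. Its sample size reproduces: 2 × (1.960 + 0.842)² / 0.5² = 62.8, so 63 per arm. Section 2.11.2 excludes participants with missing data. With 75 per arm and 20%–25% dropout, that leaves 75 × 0.80 = 60 to 75 × 0.75 = 56 per arm.

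**Count of simple indirect effects.**

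- Mediators: PCS, TSK, PIPS, R-NPQ = 4.
- Outcomes: FIQR, pain, fatigue, HADS-A, HADS-D, PSS, CSI, PF-SF-36, B-PSQI, MISCI = 10. PGIC/PSIC is measured once and has no change score.
- Contrasts = 3; windows = 2.
- 4 × 10 × 3 × 2 = 240. With HADS as one score, 4 × 9 × 3 × 2 = 216.
- Distinct treatment-to-mediator paths: 4 × 3 × 2 = 24.
- Not counted: the multiple-mediator models, and seven biomarkers in the follow-up window (up to 7 × 10 × 3 = 210).

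**Family-wise error.** Because the effects share paths, 1 − 0.95^240 (about 1.00) does not apply. The rate was therefore simulated with three arms including the shared TAU arm, no treatment effect on any mediator or outcome, the indirect effect as the product of the two paths, and 1,000 bootstrap resamples. Each scenario had 1,500 simulated trials, so the Monte Carlo standard error at 0.78 is √(0.78 × 0.22 / 1500) = 0.011. All correlations are assumptions; the between-outcome correlation is 0.5 throughout.

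| Mediator–mediator / mediator–outcome / between-window correlation | P(≥1 false), bias-corrected | Same, after a Pearson screen | P(≥1 false), percentile |
|---|---|---|---|
| 0.5 / 0.3 / 0.6 (base) | 0.78 | 0.78 | 0.56 |
| 0.3 / 0.3 / 0.5 | 0.83 | 0.83 | 0.62 |
| 0.7 / 0.5 / 0.7 | 0.61 | 0.61 | 0.47 |
| 0.8 / 0.3 / 0.8 | 0.60 | 0.60 | 0.40 |
| 0.5 / 0.5 / 0.6 | 0.70 | 0.70 | 0.56 |
| 0.5 / 0.1 / 0.6 | 0.65 | 0.60 | 0.35 |
| 0.5 / 0 / 0.6 | 0.48 | 0.37 | 0.19 |

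The table uses 60 per arm. The base case gives 0.76 at both 56 and 75 per arm.

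**Per-effect error.** At mediator–outcome correlations of 0.3–0.5, the bias-corrected interval excluded 0 in 7.0%–8.0% of null effects and the percentile interval in 4.5%–5.6%. A separate simulation at 58 per arm gave about 7.5%–9% and 5%–6%. In the base case 240 × 0.0778 = 18.7 effects are falsely significant on average.

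**Cross-check with a simpler test.** Requiring both paths to be significant at 5% is closer to the percentile interval and gives lower values. Across separate runs with mediator–outcome correlations of 0.3–0.5, the chance of at least one false effect was 0.37–0.59. Raising the per-path level to 7%–7.5%, to mimic the bias-corrected interval, gave 0.47–0.72.

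**Effect of an adjustment.** Using the joint test on the 240 effects at 60 per arm, with mediators related to outcomes, the unadjusted chance of a false finding was 0.45–0.58. Benjamini–Hochberg over all 240 brought it to 0.03–0.04.

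**One contrast alone.** FIBRO-On vs FIBRO-Out has 4 × 10 × 2 = 80 effects. At 58 per arm (400 simulated trials per scenario, mediator correlations 0.3–0.8, mediator–outcome correlations 0.2–0.4), the chance of at least one false effect was 0.31–0.49. When any occurred, about 10–23 of the 80 occurred together.

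**The case against.** Several points on the other side have force.

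- **No trial-level rule is stated.** A reader might infer that any single interval excluding 0 settles objective 3. The protocol does not say so: it defines significance per parameter. The family-wise problem follows from the absence of a family or hierarchy.
- **Scope of Benjamini–Hochberg.** The sentence in 2.11.1 has no limiting words, so restricting it to clinical endpoints is inferred from its place. But 2.11.2 then gives its own criterion, and a nominal 95% CI excluding 0 is not an adjusted decision. If the correction was meant to reach mediation, the two sections still need reconciling.
- **The null is a worst case for the TAU contrasts.** The introduction reports earlier FIBROWALK improvements in kinesiophobia, so some mediators may truly respond. The unadjusted rule would still apply to each mediator and contrast that does not. For FIBRO-On vs FIBRO-Out, which Table 1 describes as equivalent in content, no difference on the mediators is plausible.
- **The Pearson step.** The protocol computes mediator–outcome correlations first but does not say that they gate the path models. Used as a screen, they leave the correlated scenarios at 0.60–0.83.
- **The second window reads as supplementary.** That is fair, but 2.11.2 applies the same rule to it.
- **Detail may sit in an analysis plan that is not shown.** That would excuse silence. Here the article fixes the rule and the interval type itself.

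**Conclusion.** The point stands in limited form. Section 2.11.2 fixes an unadjusted per-effect rule over about 240 simple indirect effects (216 with HADS as one score) and designates no primary family.

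The chance of at least one false significant indirect effect is about 0.60–0.83 under the planned interval. This rests on two assumptions: no treatment effect on any mediator, and mediator–outcome correlations of 0.1–0.5, which the documents do not supply. Without that correlation it is about 0.48, so it would be wrong to infer that a false finding is more likely than not whatever the mediators do. The bias-corrected interval adds a separate, smaller inflation: about 7–9% per effect rather than 5% at correlations of 0.3–0.5.

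Nor do the figures show that the rule cannot tell a real mediator from noise. Single tests are only moderately above nominal; what is missing is control over the set. The primary FIQR and cost-utility analyses are unaffected.

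**What to change.** Amend section 2.11.2 as follows:

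1. Designate a small primary mediation family. One example is FIQR at 6 months, the four process mediators, and each active arm vs TAU: 4 × 2 = 8 indirect effects. The exact choice is the sponsor's.
2. Apply the Benjamini–Hochberg correction already used in 2.11.1 to that family, with bootstrap p-values. A small family still needs it: eight independent tests at 5% would give 1 − 0.95^8 = 0.34.
3. Use percentile rather than bias-corrected bootstrap intervals. This restores a per-effect error near 5% but does not replace step 2, since the unadjusted percentile figures over 240 effects are still 0.35–0.62 when mediators correlate with outcomes.
4. Label all other outcome, contrast, window and biomarker mediation models exploratory. Report their estimates and intervals without calling them significant on the interval alone.

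The change is to wording only and needs no new data. The cost is some loss of power for individual mediators.
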